## Abstract

**Background:**

Arterial access is a major site of bleeding complications after invasive coronary procedures. Among strategies to decrease vascular complications, the radial approach is an established one. Vascular closure devices provide more comfort to patients and decrease hemostasis and need for bed rest. However, the inconsistency of data proving their safety limits their routine adoption as a strategy to prevent vascular complications, requiring evidence through adequately designed randomized trials. The aim of this study is to compare the radial versus femoral approach using a vascular closure device for the incidence of arterial puncture site vascular complications among non-ST-segment elevation acute coronary syndrome patients submitted to an early invasive strategy.

**Methods:**

ARISE is a national, multicenter, non-inferiority randomized clinical trial. Two hundred patients with non-ST-segment elevation acute coronary syndrome will be randomized to either radial or femoral access using a vascular closure device. The primary outcome is the occurrence of vascular complications at an arterial puncture site 30 days after the procedure, including major bleeding, retroperitoneal hematoma, compartment syndrome, hematoma ≥ 5 cm, pseudoaneurysm, arterio-venous fistula, infection, limb ischemia, arterial occlusion, adjacent nerve injury or the need for vascular surgical repair.

**Results:**

Enrollment was initiated in September 2012, and until October 2013 91 patients were included. The inclusion phase is expected to last until the second half of 2014.

**Conclusions:**

The ARISE trial will help define the role of a vascular closure device as a bleeding avoidance strategy in patients with NSTEACS.

**Trial registration:**

ClinicalTrials.gov identifier: NCT01653587

## Background

Antithrombotic therapy and percutaneous or surgical myocardial revascularization procedures represent the basis of hospital treatment for patients admitted with non-ST-segment elevation acute coronary syndrome (NSTEACS) [1,2]. However, the desired reduction of ischemic event recurrence is accompanied by an increased incidence of bleeding [3,4]. Initially tolerated as an inherent complication of anti-ischemic treatment, major bleeding is now recognized as a predictor of mortality and adverse ischemic outcomes [5]. In fact, NSTEACS patients who develop major bleeding have a two- to ten-fold increase in mortality after a one-year follow-up [6,7]. In the Acute Catheterization and Urgent Intervention Triage Strategy (ACUITY) trial [8] involving 13,819 NSTEACS patients submitted to an early invasive strategy and randomized for antithrombotic treatment with unfractionated heparin (UFH) plus IIb-IIIa glycoprotein receptor inhibitor (GPI), bivalirudin plus GPI or bivalirudin alone, the prognostic impact of major bleeding was comparable to that of acute myocardial infarction (AMI) in subsequent mortality (11.7% versus 9.1%, respectively) [9]. Randomized clinical trials involving NSTEACS patients show major bleeding rates varying from 2% to 5% [5,8], approaching the prevalence of refractory ischemia, AMI or deaths observed in these studies. A publication of the National Cardiovascular Data Registry Acute Coronary Treatment and Intervention Outcomes Network Registry Get with the Guidelines (NCDR ACTION Registry-GWTG) [10], a representative registry of real world practice, has evaluated 72,699 unselected patients with NSTEACS and 48,943 patients with ST-segment-elevation AMI evaluated at 360 North American hospitals between January 2007 and June 2009. Authors have reported a major bleeding rate of approximately 9% among NSTEACS patients and 12% among those with ST-segment-elevation AMI, primarily influenced by the presence of comorbidities such as older age, female gender, chronic renal failure, as well as the use of invasive techniques [9,11].

### Bleeding and vascular complications related to arterial access

Because arterial puncture followed by sheath insertion using the modified Seldinger technique [12] has become the standard method used to perform invasive cardiovascular procedures, vascular access has become a major site of bleeding complications [13]. According to the Global Registry of Acute Coronary Events (GRACE), the most frequent bleeding sites were gastrointestinal (31.5%) and those related to vascular access (23.8%), with the latter being more prevalent among patients submitted to invasive strategies [11]. In a joint analysis of 17,393 acute coronary syndrome (ACS) patients submitted to percutaneous coronary intervention (PCI) and included in the studies Randomized Evaluation in PCI Linking Angiomax to Reduced Clinical Events (REPLACE) - 2, ACUITY and Harmonizing Outcomes with RevascularIZatiON and Stents in Acute Myocardial Infarction (HORIZONS-AMI), the bleeding prevalence by Thrombosis in Myocardial Infarction (TIMI) criteria was 5.3%, of which 2.1% (38.6%) were related to vascular access [14].

### Strategies to prevent bleeding and vascular complications

#### Radial technique

Among the strategies to decrease vascular complications after invasive coronary procedures, the radial approach is an established one [15,16]. Although it has been adopted by only a few centers, it provides more comfort to patients, allows early ambulation, decreases hospital stay and shows less vascular puncture site complications [17]. In a comparative randomized trial between radial and femoral techniques involving 7,021 ACS patients submitted to invasive techniques, both techniques were shown to be safe and effective for PCI, with similar incidences of death, AMI, stroke and major bleeding at 30 days (3.7% versus 4.0%; *P* = 0.50) [18]. However, the radial approach displayed significantly decreased vascular complications, including pseudoaneurysm, large hematomas, arterio-venous fistula and limb ischemia requiring surgical intervention (1.4% versus 3.7%; *P* < 0.0001).

Given the small number of training centers that use the radial technique, the uncertainties concerning the learning curve which would be associated with a higher failure rate and more radiological exposure, and the lack of large-scale multicenter studies that can reproduce the excellent results obtained by highly experienced centers, the femoral approach remains the most popular for invasive coronary procedures [19].

#### Percutaneous vascular closure devices

Although the real prognostic significance of preventing vascular access complications and minor bleedings has not yet been established, the occurrence of vascular access complications is associated with poor patient adherence to the antiplatelet therapy after hospital discharge and is a major and known predictor of ischemic complication recurrence [20]. Strategies to decrease femoral access vascular complications have been frequently evaluated and implemented, such as the use of smaller diameter endovascular devices, early arterial sheath removal, fluoroscopy or ultrasound-guided femoral puncture and the choice of antithrombotic agents with better safety profiles [8,21-23].

Since 1995, percutaneous femoral vascular closure devices (VCD) were introduced to decrease vascular complications, hemostasis and ambulation times of patients submitted to invasive procedures by femoral access. Although these devices have been rapidly incorporated into interventionist practice, they have shown conflicting results regarding their safety and efficacy, motivating a class III recommendation as a strategy to decrease vascular complications in a recent position taken by the American Heart Association [24].

Three meta-analyses that compared VCD and manual compression from 2004 have reported conflicting results regarding their safety. Koreny *et al*. [25] grouped data from 30 randomized trials involving 4,000 patients and showed a decrease of 17 minutes to obtain hemostasis with VCD, at the expense of a non-significant increase in hematomas, bleeding, arterio-venous fistulas and pseudoaneurysms. Nikolsky *et al*. [26] identified 30 randomized and observational studies in 37,066 patients where VCD were associated with increased vascular complications compared with manual compression, particularly using the VasoSeal (Datascope Corp., Montvale, NJ) device. Conversely, Vaitkus *et al*. [27] described in a meta-analysis involving 15 randomized trials and 5,084 patients a decrease in vascular complications favoring the new technology, particularly when using AngioSeal (St. Jude Medical, St. Paul, MN) and Perclose (Abbott Vascular, Redwood City, CA) devices, an observation that has been validated by results of large multicenter observational registries published subsequently [28,29].

In summary, different VCD, although not demonstrating a class effect, clearly provide more comfort to patients, decreasing hemostasis and bed rest time. However, the inconsistency of data proving their safety limits their routine adoption as a strategy to prevent vascular complications, requiring evidence through adequately designed randomized studies. The hypothesis of this investigation is that among NSTEACS patients submitted to an early invasive strategy and randomized to the femoral or radial approach, the percutaneous femoral vascular closure device would decrease the prevalence of vascular complications at the puncture site, thus fulfilling the non-inferiority criteria compared with radial access.

## Methods

### The ARISE study

#### Design

ARISE is a national, multicenter, non-inferiority randomized clinical trial comparing the radial versus femoral approach using VCD to decrease vascular complications related to an arterial puncture site among NSTEACS patients submitted to an early invasive strategy (Figure 1). The primary outcome will be evaluated from randomization until 30 days after the invasive coronary procedure.

**Figure 1 F1:**
[figure not shown]
ARISE study design: a randomized trial of the radial versus femoral approach using AngioSeal in non-ST-segment elevation acute coronary syndrome (NSTEACS) patients.

#### Outcomes

##### Primary outcome

Vascular complications at the arterial puncture site 30 days after the procedure (vascular complications at the arterial puncture site include major bleeding, retroperitoneal hematoma, compartment syndrome, hematoma ≥ 5 cm, pseudoaneurysm, arterio-venous fistula, infection, limb ischemia, arterial occlusion including asymptomatic occlusion, adjacent nerve injury or the need for vascular surgical repair).

##### Secondary outcomes

Individual components of the primary outcome, hematoma < 5 cm, major bleeding unrelated to the puncture site or myocardial revascularization surgery, device success and crossover rate; cardiovascular death, AMI or stroke at 12 months of evolution.

Study outcome definitions are listed in Table 1. A committee of clinicians will adjudicate all primary outcomes.

**Table 1 T1:** Outcome definitions

**Term**	**Definition**
Major bleeding	Type 3 ((3a) bleeding with hemoglobin drop ≥ 3 and < 5 g/dL, or packed red cells transfusion; (3b) bleeding with hemoglobin drop ≥ 5 g/dL, heart tamponade, bleeding requiring surgical intervention or bleeding requiring intravenous inotropic drugs; (3c) intracranial hemorrhage; subcategories confirmed by autopsy, imaging examinations or lumbar puncture; intraocular bleeding with vision impairment) or type 5 bleeding ((5a) possibly fatal bleeding, (5b) definitive fatal bleeding), according to the Bleeding Academic Research Consortium definition [30].
Retroperitoneal hematoma	Defined as building up of blood in the retroperitoneal space, caused by common femoral artery puncture above the inguinal ligament, not obtaining an adequate hemostasis with consequent hematoma formation. It is clinically manifested by dorsal, loin or inguinal pain, hypotension and/or hematocrit drop. Its diagnosis has to be confirmed by abdominal ultrasound and/or CT.
Compartment syndrome	Defined as abnormal tissue pressure increase inside an osteo-fascial compartment (considering in this analysis the involvement of upper or lower limbs after arterial puncture), impairing nervous and muscular structure irrigation, characterized by paresthesia, continuous pain, hypoesthesia, edema and stiffening of the affected region, peaking with tissue necrosis and/or permanent functional injury if not adequately treated.
Hematoma	Defined as localized collection of extravascular blood adjacent to the vessel, located in the topography of the punctured artery used to perform the procedure.
Pseudoaneurysm	Defined as a neocavity delimited by tissues adjacent to the injured vessel, fed by continuous blood flow into and out, coming from the real lumen through a narrow neck connecting it to the inside of the cavity. Diagnosis is determined by the presence of a pulsating bulge close to the puncture hole and is confirmed by duplex scanning.
Arterio-venous fistula	Defined as an abnormal and acquired communication between the arterial and venous surface caused by the inadvertent puncture of a vein adjacent to the femoral or radial artery. Diagnosis is determined by the presence of a continuous murmur or thrill at the puncture site and is confirmed by duplex scanning.
Infection	Defined as the introduction and/or colonization of microorganisms in structures adjacent to the puncture site and/or blood flow, predisposed by difficult access, repeated punctures, long introducer stay, multiple catheters or a prolonged procedure. It is manifested by pain, hyperemia, local edema, adenopathy, fever and/or leukocytosis with a shift to the left in the blood count.
Limb ischemia	Defined as the presence of signs and/or symptoms such as local pain, paresthesia, paresis, skin pallor, cyanosis, lack of pulse, cold extremities and/or muscle tenderness, caused by acute or sub-acute arterial occlusion and confirmed by duplex scanning and/or arteriography.
Asymptomatic arterial occlusion	Defined by blockade of the arterial blood flow without manifestations of disturbance of the cell mechanism or insufficient tissue blood supply, not involving the terminal arterial segment (example: radial artery occlusion).
Adjacent nerve injury	Defined by the presence of sensory and/or motor disorders in the limb through which the invasive coronary procedure was performed, with persistence of signs and/or symptoms for ≥ 24 hours, as a consequence of direct injury by inadvertent nerve puncture, excessive compression or extrinsic compression by a hematoma and/or a pseudoaneurysm.
Vascular surgical repair	Defined by the presence of complications at the arterial puncture site requiring immediate or late (first 15 days) surgical intervention to prevent and/or minimize sequelae to the affected limb.

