**Drug**				
Aspirin	300 mg orally	No	100 mg per day orally	100 mg per day orally, indefinitely
Clopidogrel	600 mg orally	No	75 mg per day orally	75 mg per day orally, 12 months
Prasugrel	60 mg orally	No	10 mg per day orally	10 mg per day orally, 12 months
Ticagrelor	180 mg orally	No	90 mg twice daily orally	90 mg twice daily orally, 12 months
Enoxaparin	1 mg per kg SC	0.3 mg per kg IV if the last dose is 8 to 12 hours 0.5 to 0.75 mg per kg IV if the last dose is >12 hours	1 mg per kg SC twice daily	No
Fondaparinux	2.5 mg SC	85 UI per kg IV UFH or 60 UI per kg IV UFH if GPI is scheduled	2.5 mg/SC/day	No
Abciximab	No	Intravenous loading dose of 0.25 mg per kg	0.125 mcg per kg per min for 12 hours, IV, without using HNF	No
Tirofiban	No	Intravenous loading dose of 25 mcg per kg	0.15 mcg per kg per min for 12 to 18 hours, IV, without using HNF	No

GPI, IIb-IIIa glycoprotein receptor inhibitor; UFH; unfractionated heparin, IV, intravenous; SC subcutaneous.

Electrocardiogram (ECG), CK-MB and/or troponin, glucose, creatinine, sodium, potassium, blood count and coagulation tests shall be obtained before patient randomization. Biomarkers (CK-MB and/or troponin) shall be checked between 12 and 24 hours after the procedure. ECG shall be performed soon after the procedure and within 12 to 24 hours after the procedure or when a new ischemic event is suspected. Hemoglobin and hematocrit dosage will be required in the presence of vascular complications or bleeding. Vascular and systemic complications related to the arterial vascular access will be evaluated in the interval between procedure completion, hospital stay and the first 30 days of evolution, through a scheduled visit. Other outcomes will be considered until the 30 days of evolution, with late follow-up by a visit or telephone call regarding cardiovascular death, AMI or stroke, at 12 months.

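### Table 1 counts vascular surgical repair only in the first 15 days, while the primary composite that contains it runs to 30 days after the procedure

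*Protocol article*

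**What the plan says.** Four places in the protocol article bear on the window.

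- **Primary outcome** (and, in the same sense, the Abstract) sets the time point: "Vascular complications at the arterial puncture site 30 days after the procedure". The list of components ends with "adjacent nerve injury or the need for vascular surgical repair".
- **Design** gives a start and an end: "The primary outcome will be evaluated from randomization until 30 days after the invasive coronary procedure".
- **Table 1, entry on vascular surgical repair** restricts that component to puncture-site complications "requiring immediate or late (first 15 days) surgical intervention". It does not say what the 15 days are counted from.
- **The assessments paragraph after Table 3** says that access-related complications "will be evaluated in the interval between procedure completion, hospital stay and the first 30 days of evolution, through a scheduled visit".

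Table 1 is operative text. The Secondary outcomes section says "Study outcome definitions are listed in Table 1. A committee of clinicians will adjudicate all primary outcomes". The same section makes each component of the primary outcome a secondary outcome, so repair is also to be reported by itself.

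**The concern.** The article gives two end dates for one component of its primary outcome. A committee that applies Table 1 literally would not record a repair on day 20 as a repair event. A reader of the Primary outcome section would expect it to be recorded. This is a conflict between two stated rules, not a detail left to a fuller document.

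What is at stake is mainly the repair count as a secondary outcome: it would be presented beside a 30-day composite but cover a shorter period. A lesser matter is the start of the window, which is randomization under Design and the end of the procedure in the assessments paragraph.

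**Working it through.** The article states no figure for this point, so the check sets the texts side by side.

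**1. End of the window**

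| Place | Applies to | End |
|---|---|---|
| Abstract; Primary outcome | composite, including repair | 30 days after the procedure |
| Design | primary outcome | 30 days after the procedure |
| Assessments paragraph | access-related complications | first 30 days |
| Table 1 | repair component | first 15 days, origin not stated |

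The two categories in Table 1 are immediate repair and late repair, and the bracket bounds the late one. A repair after day 15 fits neither.

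**2. Is the limit peculiar to repair?** Yes. The Primary outcome section lists eleven components: major bleeding, retroperitoneal hematoma, compartment syndrome, hematoma of at least 5 cm, pseudoaneurysm, arterio-venous fistula, infection, limb ischemia, arterial occlusion, nerve injury and repair. In Table 1 only repair has an upper time limit. The 24 hours under nerve injury is a minimum duration of signs or symptoms.

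**3. Days left uncovered.** This depends on day 0, which has to be assumed.

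- Counted from the procedure: 30 − 15 = 15 days uncovered (days 16 to 30), or 15/30 = half of the window.
- Counted from randomization, with the procedure k days later: the limit falls 15 − k days after the procedure, leaving 30 − (15 − k) = 15 + k days. If the procedure takes place within the planned 72 hours of admission, k is at most 3, so at most 18 days.
- Counted from recognition of the complication on day d after the procedure: the limit falls on day d + 15, leaving 15 − d days, and none once d reaches 15.

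The range is therefore 0 to 18 days. The procedure is the most natural origin, since every other end date refers to it. These are days of follow-up, not events.

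**4. Does the composite lose events?** Table 1 defines repair as following from a complication at the puncture site, so a patient repaired on days 16 to 30 has such a complication by definition. The other ten components have no day limit within the 30-day window, and major bleeding includes bleeding that requires surgery. The composite loses a patient only if the lesion behind the late repair meets none of those ten. This is possible, for example a hematoma under 5 cm that is operated on but not classed as major bleeding, but it should be unusual.

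**5. Does the repair count lose events?** Yes, directly. Under the literal definition, every repair after the limit is absent from the secondary outcome, whatever else the patient has.

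**6. Start of the window.** Design starts at randomization; the assessments paragraph starts when the procedure ends. Because a puncture-site complication cannot precede the puncture, the two differ in practice only by the procedure itself.

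**The case against.** The strongest reply is that the mismatch has almost no consequence. Late repair presupposes a lesion that is normally already counted, so the primary result should hardly move. Repair is one of eleven components and has no hypothesis or power of its own. A count under a stated 15-day definition is narrower than the composite's window, but not wrong in itself. On the start of the window, Design is explicit, and the assessments paragraph follows the laboratory and ECG timetable and refers to a visit. It can fairly be read as a schedule of examinations, not as a rule that discards events during the procedure. Most lesions arising then would still be present when it ends.

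Most of this stands. It limits the effect and makes the start of the window a wording matter. It does not remove the conflict: Table 1 and the Primary outcome section still classify the same late repair differently, and no reason is given for treating repair as an exception.

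A reader might be tempted to go further in three ways, none of which the article supports.

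- *That the lost events bias the trial toward non-inferiority.* The definition applies alike to both arms, and the article gives no repair rate or timing by arm. By step 4 of the working, the composite would seldom lose an event at all.
- *That the result could shift by about one percentage point.* With 97 per group, 1/97 = 1.0 point is what any single reclassified event in any component would do to that arm's rate. It does not show that this definition reclassifies even one primary event.
- *That repair is the most serious component.* Table 1 includes fatal bleeding under major bleeding.

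**Conclusion.** The point holds as an inconsistency in an outcome definition. Table 1 stops counting surgical repair after 15 days with no stated day 0, while the primary composite that includes repair runs to 30 days after the procedure. Assuming that the 15 days count from the procedure, days 16 to 30 are uncovered, and repair as a secondary outcome would be undercounted relative to the stated window.

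The effect on the primary composite is probably small. That judgment rests on the underlying lesion usually meeting another component without a day limit. The number of patients affected is unknown. Confidence is high for the textual conflict; no effect on the non-inferiority conclusion is claimed. The difference in starting points is minor.

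**What to change.** - **Table 1, vascular surgical repair:** replace the 15-day limit with surgical repair within 30 days of the procedure, in line with Design and Primary outcome.
- **Assessments paragraph (minor):** use the window given under Design for all components in both arms, from randomization, and so including the procedure itself, to 30 days after the procedure.

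The cost is one line in each place. No new data collection should be needed, because a scheduled visit for the first 30 days is already planned. Since 91 patients had been included by October 2013, the change should be made before the analysis, and any repair already adjudicated under the 15-day limit should be read again under the 30-day one.
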